## Abstract

**Background:**

In addition to recuperating from the physical and emotional demands of childbirth, first-time mothers are met with demands of adapting to their social roles while picking up new skills to take care of their newborn. Mothers may not feel adequately prepared for parenthood if they are situated in an unsupported environment. Postnatal psychoeducational interventions have been shown to be useful and can offer a cost-effective solution for improving maternal outcomes.

**Objective:**

The objective of this study was to examine the effectiveness and cost-effectiveness of Web-based and home-based postnatal psychoeducational programs for first-time mothers on maternal outcomes.

**Methods:**

A randomized controlled three-group pre- and posttests experimental design is proposed. This study plans to recruit 204 first-time mothers on their day of discharge from a public tertiary hospital in Singapore. Eligible first-time mothers will be randomly allocated to either a Web-based psychoeducation group, a home-based psychoeducation group, or a control group receiving standard care. The outcomes include maternal parental self-efficacy, social support, psychological well-being (anxiety and postnatal depression), and cost evaluation. Data will be collected at baseline, 1 month, 3 months, and 6 months post-delivery.

**Results:**

The recruitment (n=204) commenced in October 2016 and was completed in February 2017, with 68 mothers in each group. The 6-month follow-up data collection was completed in August 2017.

**Conclusions:**

This study may identify an effective and cost-effective Web-based postnatal psychoeducational program to improve first-time mothers’ health outcomes. The provision of a widely-accessed Web-based postnatal psychoeducational program will eventually lead to more positive postnatal experiences for first-time mothers and positively influence their future birth plans.

**Trial Registration:**

International Standard Randomized Controlled Trial Number (ISRCTN): 45202278; http://www.isrctn.com/ISRCTN45202278 (Archived by WebCite at http://www.webcitation.org/6whx0pQ2F).

## Introduction

The period following a child’s birth is considered the most crucial period for mothers as they venture from their current-known reality to an unknown new reality. In addition to recuperating from the physical and emotional demands of childbirth, first-time mothers are concurrently confronted with challenges associated with the demands of adapting to their social roles as new parents [1]. In addition, they are required to pick up new skills to take care of their newborn [2]. The subsequent mastery of these necessary skills at home, without the support from health care professionals, may be challenging for some. This change in role from a nonparent, being only responsible for oneself, to having added responsibility in caring for their newborn could take a toll on first-time mothers if their expectations do not match their experiences [3]. According to the theory of maternal role attainment, a mother’s emotional outcome during this phase is very much influenced by the mother’s biopsychosocial being, family, and the environment that she is surrounded by [4]. Often, mothers are situated in an unsupported environment and may not feel adequately prepared for motherhood. This presents as a challenge physically, emotionally, and socially, and this is particularly so for first-time mothers [5]. The early postpartum phase presents a critical period where mothers prepare themselves for parenting. A mother’s negative psychological status and well-being influence the type of parenting given to their newborn in their developmental stages, consequently impairing the mother-infant relationship and impacting the child’s outcome [6].

### Postnatal Services in Singapore and Underused Antenatal Classes

To support mothers, antenatal classes and postnatal support are largely provided by the polyclinics and maternity hospitals in Singapore [7]. Antenatal classes are spread over several weeks and are usually conducted by nurses or midwives from maternity wards or private hospitals. A systematic review revealed that midwifery-led care was associated with better maternal outcomes and should be encouraged [8]. First-time mothers find that being able to communicate with a midwife regarding issues not only helped develop a trusting relationship but also helped to promote choice and control, making them feel more prepared for parenting [9]. Mothers were also satisfied with midwifery-led care [10]. However, antenatal classes usually come with a high price tag in Singapore, which mothers from lower socioeconomic backgrounds may not have access to. In contrast, such classes in certain countries in Western Europe have been offered to mothers without a fee [11]. Research also suggests that the home services provided to mothers are associated with improved emotional maternal outcomes and satisfaction [12].

### Challenges Surrounding Postnatal Period

The average length of hospital stay post delivery is approximately 24 to 72 hours for normal deliveries across all maternity hospitals in Singapore [13]. During the transitional period from hospital to home, mothers face physical challenges, including fatigue from lack of sleep. Mothers often feel a lack of support from 1 to 3 weeks after their discharge [14]. The reality of caring for their newborn only sets in after they are discharged and on their own, and this is when most learning needs are found [15]. Hence, there is a gap in the spectrum of care from the point of discharge back to their homes.

### Postnatal Depression

Postnatal depression (PND) is a depressive illness of mild to moderate severity that occurs during the first postnatal year [16]. It is one of the most common health issues that occurs among postnatal mothers globally, with most mothers experiencing PND in the first 3 months of the postnatal period [17]. In an earlier meta-analysis based on 59 studies, the prevalence of PND was approximately 13% [18]. In a recent meta-analysis of 18 studies, the overall prevalence was 20% [19], whereas another meta-analysis of 78 studies reported an overall prevalence of 3.1% [20]. The prevalence of PND in Singapore is 6.8% [21]. A local study suggested that mothers might be vulnerable to emotional distress cross-culturally regardless of their cultural postnatal traditions [22].

PND is caused by an interplay of a multitude of psychological factors, including societal expectations, social connectedness, child’s temperamental challenges, a mother’s coping strategies, and many other life stressors [23]. Physiological causes also include neurochemical imbalances in the brain [24]. If left untreated, it can persist for many years [25], leaving detrimental effects on the mother’s recovery period. Moreover, there is an association between the mother’s mental health status and maternal-child bonding, which subsequently affects the development of depression in adolescence [6]. The father and the family unit are also inevitably affected, which in turn may affect the mother’s social relationships [26,27]. These challenges are important in informing health care providers for developing a service that is essential to the promotion of a positive maternal experience. Such strategies may have an impact on future fertility rates, which is important for Singapore, a country with a rapidly aging population and a very low birth rate.

### Social Support, Maternal Self-Efficacy, and Postnatal Depression

Social support refers to interpersonal relationships that provide individuals with emotional support and self-confidence for maintaining maternal and infant psychological well-being. This form of support facilitates a mother’s adjustment into motherhood [28]. It acts as a form of buffer for mothers to mediate stress. Parenting can be psychologically stressful for first-time mothers [29], but good social support from various parties can help ease the transition phase into parenthood. The primary sources of support for a mother come mostly from their partner, other family members, and friends. However, providing support for mothers by nurses and midwives during the early postnatal period is also important, as there have been consistent evidence showing that the availability of social support contributes significantly to a person’s ability to self-regulate in the presence of stressors [30-33]. A study conducted in Singapore also underlined the significance of providing competent postnatal care to first-time mothers to improve maternal outcomes [22]. Moreover, barriers to mobilizing support were also present and these include fear of judgment and feeling like a burden [34]. Hence, having a variety of support providers can help protect mothers against the harmful psychological effects of stressors related to parenting by enhancing facilitators and reducing barriers to mobilizing support.

Another crucial component in a seamless transition to parenthood for mothers is maternal self-efficacy. Maternal self-efficacy is the belief that a mother holds of her competence in achieving a set of tasks that produces results related to parenting [35]. According to Bandura’s theory of self-efficacy, perceptions of self-efficacy come from four main sources of feedback: mastery experience, vicarious experiences, verbal persuasion, and emotional arousal [36]. For example, in the proposed study, mastery experience means the ability to strengthen self-motivation following successes in performing baby care or self-care tasks. Vicarious experiences refers to acquiring a skill through modeling from peer mothers, hence persuading herself that she, too, is able to carry out the task. Verbal persuasion is the belief that they are able to cope with baby care through encouragement from others. Emotional arousal is the psychological state of mind attributed with performing a task. Bandura’s self-efficacy theory postulates that one’s self-efficacy operates to reduce feelings of stress and depression and is crucial in determining one’s emotional reaction toward a situation.

The amount of social support received and the level of maternal self-efficacy have an impact on a mother’s emotional well-being. Inconsistent or low levels of social support have been found to be strongly associated with PND [34]. A study conducted in Canada reported the importance of social support in reducing PND [37]. Other research studies have also found that poor self-efficacy among mothers and a lack of social support are strongly associated with PND [21,38-41]. These studies support that self-efficacy, social support, and PND are associated variables, which are important in determining maternal outcomes. However, only one study has evaluated their relationships in first-time mothers, which confirmed their interrelated relationship and that all three components should be addressed [40].

### Home-Based Psychoeducation Intervention

To combat psychological stressors from parenting, psychoeducational programs aim to address knowledge deficit regarding the postnatal period and build on the participants’ strengths and resources to promote emotional coping and parenting skills development [42]. Several studies have shown that psychoeducation programs have been one of the crucial interventions to enhance maternal self-efficacy antenatally and postnatally to improve maternal outcomes [43-45]. In 2012, a preliminary study was conducted in Singapore, which reported self-efficacy improvement and PND reduction in mothers receiving a home-based psychoeducational intervention [46]. Another study exploring women’s experiences of midwifery home visits revealed that women felt vulnerable in the early postpartum period but also felt that having a personal relationship with a midwife was important [47]. However, with the shortage of midwives and nurses, a home-based intervention might not be the most accessible and cost-effective method of delivering care.

### Accessible and Cost-Effective Web-Based Psychoeducational Intervention

A Web-based intervention might be able to address the above problem by increasing accessibility and reducing costs associated with home visits without compromising the effectiveness of a psychoeducational intervention on maternal outcomes. A meta-analysis reported the effectiveness of a Web-based intervention in achieving positive outcomes for individuals [48]. Moreover, studies have shown that socioeconomic status, including low education and low income, increases the risk of first-time mothers developing depressive symptoms [49]. Therefore, examining the cost-effectiveness of a Web-based psychoeducational intervention may help to keep costs to a minimum and to make it affordable to all mothers regardless of socioeconomic status while achieving positive maternal outcomes. Moreover, in Singapore, the Home Access Program allows lower income households to be able to afford fiber broadband connectivity and a tablet at a subsidized rate, thereby increasing accessibility to resources online [50].

### Theoretical Framework

The theoretical framework adopted for this study follows Bandura’s self-efficacy theory [36], the concepts of social support including functional and structural support that can ease a smooth progression to motherhood [40,51], as well as the interrelationships between self-efficacy, social support, and emotional well-being [52-54]. The framework used in this study is similar to the one used in our preliminary study [46]. The psychoeducation intervention programs, both Web-based and home-based, are developed to promote maternal self-efficacy, social support, and mother’s psychological well-being.

### Aims

This study aims to evaluate the effectiveness and cost-effectiveness of Web-based and home-based postnatal psychoeducational programs for first-time mothers on maternal outcomes.

### Hypotheses

The hypotheses are as follows:

When compared with mothers in the control group, mothers in Web-based and home-based psychoeducational intervention groups will report a significantly:higher level of self-efficacy,higher level of social support received,lower level of anxiety and depression, andhigher level of satisfaction with postnatal services.When compared with those in the home-based psychoeducational intervention group, mothers in the Web-based psychoeducational intervention group will not report significantly poorer aforementioned maternal outcomes.It is more cost-effective to provide a Web-based psychoeducational intervention than a home-based psychoeducational intervention and routine care.

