### Sample Size Determination

In similar studies, psychosocial and educational interventions have resulted in a medium effect size on outcomes similar to this study [44,52,62]; hence, the study intervention was regarded to have a medium size effect on outcome variables. On the basis of a power analysis, to achieve a medium effect size of 0.55, using a power of 80% and a significance level of 5% (2-sided), 52 participants would be needed in each group [63]. Although a dropout rate of 30% was reported by a previous study [52] and our preliminary study [46], we anticipated a lower dropout rate of 24% in this study because of better communication channels established with participants (eg, using social media such as WhatsApp to remind participants, follow-up questionnaire conducted through a Web-based survey). Therefore, a minimum sample of 204 (52×3/0.76) participants with 68 in each group was needed. For process evaluation, a purposive sampling of 45 participants (15 from each group) with different posttest 1 self-efficacy scores (5 high, 5 moderate, and 5 low scores from each group) were invited to participate in a process evaluation interviews, or until data saturation was achieved.

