To answer the hypothesis 1, repeated measures ANCOVA, adjusted for confounding variables (eg, age, ethnicity), will be used to test the effects of both interventions on maternal self-efficacy, social support, postnatal depression, and anxiety across four time points. Univariate ANCOVA will be used to test the difference of each of the three outcomes among three groups at each posttest time point by adjusting for confounding factors (eg, baseline data, age, and ethnicity). Chi-square test or Poisson regression will be used to determine maternal satisfaction with the postnatal supportive care at each posttest time points. To answer hypothesis 2, a 95% CI of the mean difference of maternal self-efficacy scores will be calculated. If the lower boundary is more than −5, the hypothesis will be accepted. To address hypothesis 3, we will calculate the base case incremental cost-effectiveness ratios (ICER) of the two intervention groups compared with the control group. We captured the 6-month costs at three posttest time points: (1) health care system perspectives, including service providers that mothers consumed because of maternal and/or neonatal related conditions such as GP clinic, polyclinic, private clinic, hospital out-patient, hospital Accident and Emergency and (2) participant’s out-of-pocket cost of transportation fee for these visits. In addition, fixed costs (also considered health care system perspectives) such as development and implementation of Web-based intervention, delivery of home-based intervention, and training of RAs were also captured. The effectiveness of the intervention on four outcomes (namely self-efficacy, social support, depression and anxiety) will be calculated. The ICERs for each outcome will be plotted in the cost-effectiveness plane to examine the dominance and extended dominance, and then the cost-effectiveness acceptability curves will be generated to demonstrate the cost-effectiveness of the alternatives using difference willingness-to-pay thresholds [72-78].

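### Hypothesis 2 is worded as no significant deficit on any outcome but is decided by a −5 non-inferiority rule on self-efficacy alone; the two can disagree

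*Protocol article*

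**What the plan says.** The Hypotheses section of the protocol article states, for Web against home, that "mothers in the Web-based psychoeducational intervention group will not report significantly poorer aforementioned maternal outcomes". The outcomes referred to are those listed under hypothesis 1: self-efficacy, social support, anxiety and depression, and satisfaction with postnatal services. No margin is given there.

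Under Data Analysis, hypothesis 2 is answered as follows: "a 95% CI of the mean difference of maternal self-efficacy scores will be calculated", and then "If the lower boundary is more than −5, the hypothesis will be accepted". This is the only decision rule given for hypothesis 2, and it covers self-efficacy only. The direction of the difference is not stated; the negative limit implies Web minus home.

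The Sample Size Determination section sizes the trial "to achieve a medium effect size of 0.55", "using a power of 80% and a significance level of 5% (2-sided"), so that "52 participants would be needed in each group". It mentions neither the −5 limit nor an SD for the Perceived Maternal Parental Self-Efficacy scale (PMPSE).

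**The concern.** One hypothesis has two success criteria. The wording holds unless the 95% CI for Web minus home lies wholly below 0. The rule holds when the whole interval lies above −5. An interval of −6 to +1 meets the wording and fails the rule. An interval of −4.5 to −0.5 meets the rule while Web is significantly poorer, so the plan would accept a sentence that its own data contradict.

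The scope differs too. The wording covers every outcome, whereas the rule has a margin for one. For social support, anxiety, depression and satisfaction, the only stated criterion is absence of a significant deficit. Low precision makes that easier to meet, so it cannot show that Web is no worse.

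The Discussion says that if Web is as effective as home visits and more cost-effective, it will be put to the hospital policy maker for adoption as standard care. What an accepted hypothesis 2 entitles the authors to say therefore matters.

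**Working it through.** **Inputs.** From the article: 52 evaluable per group, 68 randomised per group, limit −5, 95% CI. Assumed: the SD of PMPSE, shown over a range, and a normal distribution for the observed difference d (Web minus home), unadjusted.

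**The plan's own figure.** n = 2(1.96 + 0.842)² / 0.55² = 51.9, so 52 per group, as stated. For dropout, 52 × 3 / 0.76 = 205.3 against the stated 204, which is close enough. The sample size reproduces as a superiority calculation.

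**The two cut-offs.** Let SE = SD × √(2/n) and h = 1.96 × SE.

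- Wording met if d ≥ −h.
- Rule met if d > −5 + h.

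They coincide when −h = −5 + h, that is, h = 2.5 (a full interval width of 5 points):

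- n = 52: SD = 2.5 / (1.96 × 0.1961) = 6.50
- n = 68: SD = 2.5 / (1.96 × 0.1715) = 7.44

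Below the crossover, the only possible conflict is type A: accepted by the rule although significantly poorer. Above it, the only possible conflict is type B: not significantly poorer, yet failing the rule. The two types cannot both occur at one SD and n.

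**Worked case.** SD 6, n = 52: SE = 1.177, h = 2.31. The rule's cut-off is −2.69 and the wording's is −2.31. At a true difference of −2.5, P(−2.69 < d < −2.31) = 13%. With n = 68: SE = 1.029, h = 2.02, cut-offs −2.98 and −2.02, giving 36%.

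**Probability of conflicting verdicts.**

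| SD | n | Type | True difference 0 | True difference −2.5 |
|---|---|---|---|---|
| 6 | 52 | A | 1.4% | 13% |
| 7 | 52 | B | 2.1% | 11% |
| 8 | 52 | B | 8.5% | 29% |
| 10 | 52 | B | 25% | 51% |
| 6 | 68 | A | 2.3% | 36% |
| 7 | 68 | A | 1.1% | 9.8% |
| 8 | 68 | B | 2.1% | 11% |
| 10 | 68 | B | 14.5% | 38% |

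**Probability that each criterion is met when Web is truly 5 points worse.** By construction the rule gives 2.5% at any SD. The wording gives P(d ≥ −h | −5):

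| SD | n = 52 | n = 68 |
|---|---|---|
| 6 | 1.1% | 0.2% |
| 8 | 11% | 4.6% |
| 9.1 | 20% | 11% |
| 10 | 28% | 17% |

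The SD of 9.1 is the value at which 5 points equals the planned 0.55 SD (5 / 0.55 = 9.1). The article does not make that link, so it is an illustration only. Covariate adjustment would shrink the effective SD and move the result towards type A.

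**The case against.** The strongest reply is that the article has one decision rule for hypothesis 2, not two. The Data Analysis section gives a prespecified interval and limit in valid non-inferiority form. The sentence under Hypotheses is a one-line research hypothesis that the rule makes operational. This stands in large part. A reader might infer that the trial will treat a non-significant difference as proof that Web is no worse, with a false-claim rate several times 2.5%. The article does not support that: for self-efficacy no section says that hypothesis 2 will be judged that way, and at SD 6 the wording is stricter than the rule at a true difference of −5 (1.1% against 2.5%).

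A reader might also infer that the two criteria clash in many of the trial's possible results. That is not established either. No SD is given, and near the crossover conflict is rare: at SD 6 to 7 with 52 per arm, at most 2.1% at no true difference and at most 13% at −2.5.

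It is also fair to say that an interval between −5 and 0 can arise in any non-inferiority trial and remains possible after rewording. Only its description changes.

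What the reply does not remove is that the rule promises to accept a hypothesis whose words say something else, and that outcomes other than self-efficacy have no margin.

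**Conclusion.** The inconsistency is real and can be read directly from the two sections. The formal hypothesis claims no significant deficit on any outcome; the rule tests non-inferiority on self-efficacy. Following the plan exactly can accept a statement that the data contradict, or reject one that they do not.

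Its size is conditional on an SD that the article does not give. Conflict ranges from practically none at the crossover to 25% at no true difference and 51% at −2.5 (SD 10, 52 per arm). These figures rest on a normal approximation, unadjusted SDs, and the difference taken as Web minus home. The decision rule itself needs no change on this ground. What needs correcting is the hypothesis, and with it what an accepted result may claim.

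**What to change.** - Reword hypothesis 2, for example: *the Web-based program is non-inferior to the home-based program on PMPSE self-efficacy, that is, the lower limit of the 95% CI for Web minus home is above −5*. Drop the phrase about not being significantly poorer.
- State that a non-significant difference on any outcome will not be read as no worse. Outcomes without a margin will be reported as estimates with CIs and no non-inferiority claim. The lower-limit rule should not simply be carried over to depression and anxiety, where a higher score is worse.
- State that if the interval lies wholly between −5 and 0, the result will be reported as non-inferior by the margin but statistically poorer.

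This takes two or three sentences and no new data, and it leaves the stated rule for self-efficacy unchanged. The price is a narrower claim than the present wording suggests: one outcome, with an explicit margin.
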